**Methods and analysis:**

The Enhancing Nutrition and Antenatal Infection Treatment (ENAT) study was a 2×2 factorial, randomised clinical effectiveness study conducted in Amhara, Ethiopia from August 2020 to June 2022. We cluster-randomised pregnant women (n=2399) to receive either a nutrition intervention (iron-folic acid (IFA), iodised salt and balanced energy-protein supplementation for women with mid-upper arm circumference <23 cm) or routine care (IFA only), and individually randomised women to an infection control intervention (genitourinary tract infection screening-treatment and screening-treatment of stool parasites) or routine care (syndromic approach). Participants were followed until 1 month postpartum. A subset of 532 women-infant dyads were consecutively enrolled in the biospecimen substudy from July 2021 to August 2022. Specimens were collected at enrolment (<24 weeks) and antenatal care follow-up (third trimester), and 1–6 months postdelivery. A subset of ENAT mother–infant dyads (n=462) was enrolled in the Longitudinal Infant Development and Growth study that followed infants until 24 months postpartum, from February 2023 to June 2024. We will determine the impact of ENAT interventions on micronutrient status, inflammation biomarkers and metabolomic and microbiome profiles. We will also determine the association of these profiles with birth outcomes and infant neurodevelopment.

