## Methods

### Study setting and population

The ENAT study was conducted in 12 health centres in Amhara, Ethiopia. For ENAT, pregnant women at ≤24 weeks gestation presenting for antenatal care at the study sites were enrolled in the study if they met the eligibility criteria. Women were excluded if they had a non-viable pregnancy at ≤24 weeks gestation, determined by a lack of heartbeat on the enrolment ultrasound or were unable to return for follow-up visits (typically >2 hours travel distance from health centre). Within the ENAT study, the biospecimen substudy was conducted in a subset of six health centres (three enhanced nutrition and three routine care centres) that had functional laboratory rooms and were accessible from the regional city/central laboratory (Ambesamie, Arbgebeya, Lalibela, Legdiya, Yifag and Yismala). The LIDG study enrolled the infants born to women included in these ENAT biospecimen health centres who intended to stay in the study catchment area after giving birth. Children with major congenital anomalies, severe morbidity or developmental disorders, acute symptoms of illness (eg, headache, vomiting or dizziness) or neonatal encephalopathy were excluded from the study.

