### Study design

The ENAT study was a pragmatic, open-label 2×2 factorial, randomised clinical effectiveness study with cluster-randomisation of an enhanced nutrition package (ENP) intervention and individual-level randomisation of an enhanced infection management package (EIMP) intervention (figure 1). The detailed study protocol has been previously published^11^ and this protocol paper details the protocols for biospecimen collection and planned analysis.

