#### Intervention effects

In our primary analysis, we will examine differences in biomarkers or ’omics profiles across the randomised intervention study arms. We will use intention-to-treat as the primary analyses where individuals are analysed according to their originally assigned study arm, and in secondary analysis, we will also explore effects of individual interventions (ie, BEP) and adherence/dose. Outcomes will be compared between the primary factors (ENP or EIMP) to determine their marginal effects (ENP vs not-ENP, and EIMP vs not-EIMP). We will estimate differences in biomarkers, using linear mixed regression models. Potential confounding bias should be minimised due to the randomised study design; however, we will assess group differences in demographic and clinical characteristics at both cluster- and individual randomisation levels, as recommended by Consolidated Standards of Reporting Trials.^28^ Baseline covariate imbalances associated with both the outcome and exposure status (p<0.10) will be included in adjusted models as potential confounders. Multiple births will be excluded from analyses using birth outcomes due to the known increased rate of preterm birth and growth restriction among multiple deliveries. When large volumes of tests are conducted for metabolomics or genomics analyses, we will use the Benjamini-Hochberg method to correct for multiple testing, as appropriate.

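### The reassurance that randomisation minimises confounding does not hold for the nutrition (ENP) comparison as it does for EIMP, because women were enrolled one by one after open allocation of health centres

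*Protocol article*

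**What the plan says.** The Study design section describes ENAT as a "pragmatic, open-label 2×2 factorial, randomised clinical effectiveness study with cluster-randomisation of an enhanced nutrition package (ENP) intervention and individual-level randomisation" of the infection package. The Study setting and population section says that "pregnant women at ≤24 weeks gestation presenting for antenatal care at the study sites were enrolled in the study if they met the eligibility criteria". One exclusion there is for women who "were unable to return for follow-up visits (typically >2 hours travel distance from health centre"). The same section places the substudy in six centres, three per nutrition arm.

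The abstract says the parent trial was "conducted in Amhara, Ethiopia from August 2020 to June 2022". It also says that "A subset of 532 women-infant dyads were consecutively enrolled in the biospecimen substudy from July 2021 to August 2022".

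Under Intervention effects, ENP v not-ENP and EIMP v not-EIMP are the two primary marginal contrasts, estimated with linear mixed models. The text then states: "Potential confounding bias should be minimised due to the randomised study design". The sentence goes on to promise an assessment of group differences at both the cluster and the individual level of randomisation. The next sentence puts baseline imbalances that are associated with both outcome and exposure (p<0.10) into adjusted models.

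**The concern.** Cluster randomisation makes centres comparable in expectation. It does not by itself make the recruited women comparable when recruitment follows an allocation that can be seen. A woman's ENP arm follows from the centre where she presents, so it is fixed before eligibility and consent. The packages also look different: ENP centres gave counselling, monthly iodised salt and, below a MUAC of 23 cm, a monthly food supplement, while routine care was IFA provision. Women therefore had different reasons to attend and to agree to return. The travel criterion is qualified by a word meaning usually, which leaves some room for judgement.

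If the recruited mix differs by arm, the difference enters the ENP contrast for every biomarker and profile. A random centre effect does not remove selection that differs systematically by arm. The Benjamini-Hochberg correction deals with chance findings, not bias. Nutritional status is a plausible axis of selection, because the supplement depends on MUAC, and it lies close to the iron, iodine, inflammation and metabolomic outcomes.

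**Working it through.** The article gives no figure for this point, so there is nothing to reproduce. The passages establish the mechanism, and the arithmetic below only illustrates its possible size.

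**1. Sequence.** Parent trial start August 2020, substudy enrolment start July 2021: 11 months. Over that time an open package could have been delivered at the ENP centres before the first substudy woman was enrolled.

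**2. Which factor the reassurance fits.** EIMP is allocated to the individual woman. ENP is allocated to the centre, and the woman arrives later. Only for EIMP does randomisation bear directly on the comparison of women.

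**3. Size of a possible bias.** Assumptions, not from the article: the arms differ by 10–20 percentage points in the share of undernourished or distant women, and those women differ by 0.3–0.5 SD on the biomarker. There is no adjustment.

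Bias = difference in mix × biomarker difference = 0.10 × 0.3 = 0.03 SD, up to 0.20 × 0.5 = 0.10 SD.

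**4. Effect on a nominal 5% two-sided test.** From the article: 532 dyads and 6 centres, hence 532/6 = 88.7 per centre. Assumed: an even split, equal centre sizes, a normal approximation, and ICC 0, 0.01 or 0.05.

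- Design effect DE = 1 + (88.7 − 1) × ICC.
- SE = (2/√532) × √DE, where 2/√532 = 0.0867 SD.
- Rejection rate = 1 − Φ(1.96 − b/SE) + Φ(−1.96 − b/SE), where b is the bias.
- Effect detectable with 80% power = 2.80 × SE.

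| ICC | DE | SE (SD) | Rejection, b = 0.03 | Rejection, b = 0.10 | Detectable effect (SD) | Bias as share of detectable effect |
|---|---|---|---|---|---|---|
| 0 (clustering ignored) | 1.00 | 0.087 | 6.4% | 21.1% | 0.243 | 12–41% |
| 0.01 | 1.88 | 0.119 | 5.7% | 13.4% | 0.333 | 9–30% |
| 0.05 | 5.38 | 0.201 | 5.3% | 7.9% | 0.563 | 5–18% |

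Clustering widens the SE and lowers the excess rejection. The bias in the estimate stays the same.

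**5. Would the p<0.10 screen catch it?** Suppose a trait such as living far away has 20–40% prevalence among presenters (q). A fraction e of carriers is excluded: 30% in one arm and 0–10% in the other (assumptions). Enrolled prevalence = q(1 − e)/(1 − qe).

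- Smallest difference (q = 0.2, e = 0.1 v 0.3): 0.184 v 0.149, or 3.5 points.
- Largest difference (q = 0.4, e = 0 v 0.3): 0.400 v 0.318, or 8.2 points.

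With 266 per arm divided by DE, a two-sided test at 0.10 flags these differences with probability:

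- 0.28–0.63 ignoring clustering;
- 0.20–0.42 at ICC 0.01;
- 0.12–0.21 at ICC 0.05.

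For the larger 10-point imbalance (20–50% prevalence), the screen succeeds with probability 0.75–0.85 ignoring clustering, 0.52–0.62 at ICC 0.01 and about 0.3 at ICC 0.05.

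**6. Where an enrolment specimen exists.** Table 2 lists maternal urine, vaginal swab, serum, dried blood spot, VAMS and stool at enrolment (<24 weeks) and again at antenatal follow-up. Cord blood, infant blood, infant stool and breastmilk have no enrolment counterpart. Table 3 does not say which time points will be assayed.

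**The case against.** The best defence is the rest of the sentence. The authors hedge their reassurance, name the cluster level, and plan imbalance checks and adjustment. MUAC is measured at enrolment, so the most obvious selection axis is open to that check, and a large imbalance would often trigger adjustment. This stands in part. The plan lowers the risk, but it reaches only measured covariates that pass a screen, and the screen weakens markedly once clustering is counted.

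The article also refers readers to the separately published ENAT protocol for design detail, and safeguards may be described there. That is fair, and their absence here is not a fault. Such safeguards cannot, however, make a woman's ENP arm unpredictable from her centre.

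Two stronger readings are tempting. A reader might infer that staff and women already knew each centre's arm. The article does not date the cluster randomisation or say who knew of it; open delivery and the 11-month lag make knowledge very likely, but it remains an inference. A reader might also infer that staff used the travel exclusion at their discretion. The text gives a benchmark and softens it with one word, and nothing shows that it was applied differently by arm. Substudy enrolment was consecutive, which limits selection by staff, though not differences in attendance or consent.

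Nor do the documents support 21% as the expected false-positive rate: it needs a 0.10 SD bias, no adjustment and no clustering.

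**Conclusion.** The point holds in a limited form. The reassurance is too broad: it suits EIMP but cannot be applied in the same way to ENP v not-ENP, where recruitment followed open centre allocation. The planned checks and screened adjustment reduce the risk without removing it.

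The documents show that recruitment bias is possible, not that it occurred, and they give no basis for its size. Under the assumed 0.03–0.10 SD bias without adjustment, false-positive rates with clustering lie between about 5% and 13%. At 0.10 SD they are about 8% (ICC 0.05) to 13% (ICC 0.01). These figures rest on assumed mix differences, biomarker differences and ICCs, an even split and a normal approximation. This calls for a modest correction of wording and covariate handling. It does not invalidate the ENP comparison.

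**What to change.** 1. Limit the statement about randomisation and confounding to EIMP. For ENP, say that women were recruited after open allocation of centres and that recruitment differences are possible.
2. For maternal markers assayed at both enrolment (<24 weeks) and follow-up, adjust the ENP model for the enrolment value. Show the ENP contrast at enrolment, with its confidence interval, beside the follow-up contrast as a check on recruitment differences. Attach no rule that withholds effect claims: with three centres per arm the enrolment contrast is imprecise, and chance differences between centres also enter it.
3. For cord, infant and breastmilk outcomes, adjust ENP models for enrolment covariates named in advance, such as MUAC, in place of those selected at p<0.10. Interpret these ENP effects with the recruitment caveat.

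The cost is a little more analysis, enrolment assays for the markers concerned if they are not already planned, and a weaker causal claim for some ENP findings. Laboratory work is still described as planned, so the change can be made now.

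### Choosing covariates by p<0.10 association with arm and outcome makes the adjusted intervention-effect models data-driven and biomarker-specific, and usually leaves out a strong predictor that happens to be balanced

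*Protocol article*

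**What the plan says.** The rule stands in the protocol article, Statistical analyses, under Intervention effects: "Baseline covariate imbalances associated with both the outcome and exposure status (p<0.10) will be included in adjusted models as potential confounders". Just before it the authors say that "we will assess group differences in demographic and clinical characteristics at both cluster- and individual randomisation levels". The test behind the p-value is not described.

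The outcome model is given in one sentence: "We will estimate differences in biomarkers, using linear mixed regression models". On what is primary, the section says "We will use intention-to-treat as the primary analyses where individuals are analysed according to their originally assigned study arm". It does not say whether the unadjusted or the adjusted model carries that comparison. No covariate is named.

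The design has "cluster-randomisation of an enhanced nutrition package (ENP) intervention and individual-level randomisation of an enhanced infection management package (EIMP) intervention". The substudy uses six of the twelve health centres, three on each side of the nutrition comparison, and "A subset of 532 women-infant dyads were consecutively enrolled in the biospecimen substudy".

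Table 2 shows maternal urine, vaginal swab, serum, whole blood and stool at both the enrolment and the antenatal follow-up visit. Cord blood, infant blood, infant stool and breastmilk have no enrolment specimen.

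**The concern.** In a randomised comparison a covariate earns its place by predicting the outcome. Imbalance between arms is chance, and its p-value does not measure how much adjustment would help. The rule requires both association with arm and association with outcome, which has three consequences.

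- A strong predictor that randomisation has balanced is not brought in, so the gain in precision it offers is lost.
- Because the outcome is part of the screen, the set differs by biomarker and by factor. Across an untargeted metabolomics panel, the p-values entering one Benjamini-Hochberg correction can come from differently specified models.
- The standard error printed by the final model ignores the screening step and is not that of the procedure used.

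For the nutrition factor there is the further question of what a p<0.10 imbalance test can show with six centres.

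**Working it through.** The plan gives no power, standard deviation, intracluster correlation (ICC) or covariate correlation for the substudy, so there is no figure to reproduce.

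**Inputs.** From the protocol: n=532, six centres (532/6 = 88.7 per centre), threshold p<0.10. Assumed: covariate-outcome correlation r = 0.3, 0.5, 0.7; ICC 0.01 and 0.05; ten candidate covariates where a number is needed; two-sided alpha 0.05.

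**1. Chance imbalance.** With ten independent covariates and sound randomisation, P(at least one p<0.10) = 1 − 0.9^10 = 65%. With five it is 41%, with twenty 88%.

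**2. Infection package, one covariate.** The outcome condition is practically always met: even at r=0.3 the test statistic is about 0.3×√530/√0.91 = 7.2. The covariate therefore enters only when its standardised arm difference Z exceeds 1.645 in size, which is 10% of trials.

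In units of 4σ²/n, fixed adjustment has variance 1 − r². Under the rule the variance is (1 − r²) + k·r², where k = E[Z²; |Z|<1.645] = 0.90 − 2×1.645×0.1031 = 0.561. The ratio of rule to fixed adjustment is 1 + 0.561·r²/(1 − r²).

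When the covariate stays out, the statistic is √(1 − r²)·E + r·Z, with E an independent standard normal and |Z| capped at 1.645, yet it is judged against 1.96. Type I error is the probability that this exceeds 1.96 in size with |Z|<1.645, plus 0.10×0.05.

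| r | Variance ratio, formula | Variance ratio, simulation | Type I error, formula | Type I error, simulation |
|---|---|---|---|---|
| 0.3 | 1.06 | 1.05–1.06 | 4.7% | 4.4–4.7% |
| 0.5 | 1.19 | 1.19–1.20 | 4.0% | 3.5–4.2% |
| 0.7 | 1.54 | 1.51–1.54 | 3.0% | 3.0% |

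A simulation with one strong and nine weak covariates (4,000 runs) gave 3.9%, 3.9% and 2.6%, slightly more conservative.

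**3. Power.** The effect giving 80% unadjusted power is (1.960 + 0.842)×√(4/532) = 0.243 SD. In the ten-covariate simulation (2,000 runs) power at that effect was:

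| r | p<0.10 rule | Fixed adjustment for the strong covariate |
|---|---|---|
| 0.3 | 80% | 83% |
| 0.5 | 81% | 90% |
| 0.7 | 83% | 98% |

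**4. Nutrition package, three centres against three.**

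- Screen on centre means: the t test has 4 degrees of freedom and critical value 2.132. The smallest difference flagged is about 2.132×√[(2/3)(ICC + (1 − ICC)/88.7)], that is 0.25 SD at ICC 0.01 and 0.43 SD at ICC 0.05.
- Screen on individuals, ignoring clustering: the design effect is 1 + 87.7×ICC = 1.88 and 5.38. The chance of passing the arm condition is 2[1 − Φ(1.645/√DE)] = 23% and 48%, not 10%.
- Both conditions together, individual-level screen, ten candidates (3,000 runs): on average 1.8 and 3.6 covariates were selected, against at most one expected at the nominal 10% rate.
- With that screen and the nutrition effect then tested on the six centre means, type I error was 3.4%, against 5.0% with fixed adjustment.

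**The case against.** **The rule includes covariates; it does not say that nothing else enters.** An unseen analysis plan may name prognostic covariates, and an article need not list them. This is fair, and a missing list is not the complaint. The stated selection rule is: it is the only route into the adjusted models that the article gives, and by itself it leaves out a balanced predictor.

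**The screened analysis still beats no adjustment.** This stands. Its variance relative to the unadjusted estimator is 1 − 0.439·r², or 0.89 at r=0.5. The loss is relative to fixed adjustment, and at r=0.3 it is small (80% against 83% power).

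**Checking balance has some rationale here.** The six centres were picked for laboratory facilities and access, so balance in the nutrition comparison is not guaranteed. That supports describing the differences, but a p-value from six centres says little about them.

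Three stronger readings are tempting and are not supported.

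- A reader might infer that the primary model is the one chosen this way. The text speaks only of adjusted models and does not say which model is primary.
- A reader might infer that the rule is invalid for the nutrition factor. That needs an imbalance test that ignores clustering, which is not stated; both randomisation levels and mixed models are mentioned. In simulation, type I error rose only when the outcome model itself ignored clustering: 16% to 43% unadjusted and 12% to 33% with the rule.
- A reader might infer that comparability with the other supplementation trials is lost. The article says only that certain analyses will be coordinated, and nothing shows which covariates those trials use.

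**Conclusion.** The point holds as a matter of precision and transparency. The adjusted model is settled after looking at arm and outcome data, differs by biomarker and factor, and in about 90% of trials passes over a strong covariate. For the infection package the cost is a variance about 5% to 50% above fixed adjustment, with type I error of about 3% to 4.7% instead of 5%. False positives do not increase. The size rests on assumed correlations of 0.3 to 0.7; an enrolment value of the same biomarker could plausibly lie in that range, but the protocol gives no figure. For the nutrition package the screen has little use on either reading: weak on centre means, over-selecting on individuals. That the article leaves open which model leads makes this worse, since each biomarker then has two candidate estimates.

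**What to change.** Replace the sentence with covariates fixed in advance for their expected prognostic value, the same for all biomarkers of one specimen type:

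- For outcomes in maternal urine, vaginal swab, serum, whole blood and stool: the enrolment value of the same biomarker, plus a short list of baseline characteristics already collected.
- For cord, infant and breastmilk outcomes: the baseline characteristics only, since Table 2 shows no enrolment specimen.
- Use characteristics fixed at enrolment, not features of the later collection visit.
- Keep the list especially short for the nutrition package, because there are only six centres.

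State whether the unadjusted or the prespecified adjusted model is primary. Report baseline balance descriptively, and keep any imbalance-driven model as a sensitivity analysis.

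The cost is wording, a few degrees of freedom, and a stated rule for women without an enrolment specimen. Where an assay was planned at follow-up only, the enrolment specimen would have to be assayed too; Table 3 does not give the visits to be tested.

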#### Adverse pregnancy/child development outcomes

In our secondary analyses, we will examine the associations of biomarkers or ’omics profiles and adverse birth outcomes (eg, preterm birth, stillbirth and growth restriction) or child development outcomes (eg, EEG outcomes, MRI outcomes, eye tracking, etc). In most of these analyses, we will use a prospective cohort study design and estimate differences among birth or child development outcomes using linear or logistic regression models (based on the outcome), and adjust for covariates as relevant for specific outcomes. Details for each individual relationship examined will be included in the publications for each individual analysis.

### Patient and public involvement

The community was involved in the design of the parent ENAT study. We conducted formative research including in-depth interviews with patients and community members regarding the feasibility and acceptability of interventions as well as specific sample type collection procedures, including urine and vaginal swabs. Results of this study will be disseminated to the Ministry of Health and peer-reviewed journal publications.

